### Research questions

In this study we will compare two different incentive schemes for diabetic retinopathy screening, with a usual-care control group, to determine:Are incentives an effective strategy to encourage participation in the screening programme?While screening for diabetic retinopathy is an effective strategy for reducing blindness, to be cost-effective the screening programme requires good attendance. However, attendance rates could be improved. This study will investigate whether targeted financial incentives can increase screening participation.Does the design of the financial incentive scheme affect its effectiveness in influencing participation in health screening?There are many ways in which incentives to encourage screening participation could be delivered. Two different types of financial incentive will be compared to see which is most effective: a fixed £10 incentive, or a prize draw with a 1 in 100 chance of winning £1000.Does the choice of incentive scheme, if successful, attract patients who have a different demographic or socioeconomic status to those who attend screening regularly?A particular concern is that those in deprived socio-economic groups are less likely to attend screening [7, 30], exacerbating existing inequalities in health. By investigating the impact of our incentive schemes on the demographic profile of those who attend, we hope to learn more about the way in which incentives might be developed to target specific health inequalities. We will obtain information about age, gender, postcode and hence social deprivation status, and distance from screening center.Is offering incentives a cost-effective strategy for enhancing participation?In the current financial environment it is also important to ensure that any interventions are cost-effective. Economic evaluation using well-established economic models will be performed to determine value for money.

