#### Cost-effectiveness analysis

In order to investigate the fourth research question about the cost-effectiveness of the interventions, a health economics analysis will be conducted. The trial results will provide data on the differential rate of attendance to screening for each group. To assess the short-term cost-effectiveness of the incentives, the cost per additional screening attendee will be calculated as the cost of screening divided by the observed increase in the number of screening attendees for each pairwise comparison of groups.

A longer-term, 5 year, perspective of the cost-effectiveness of the incentives will be assessed using a Markov model. The model will assess the cost-effectiveness from the NHS perspective using the differential rates of screening attendance for each group. The long-term effects of attending screening in terms of the sensitivity of screening, treatment costs and quality of life, as well as the long-term effects of not attending screening, will be determined from the published literature. The costs across the groups will differ only in the monetary incentives provided.

The analysis pertaining to the third research question will indicate if the incentives for attending screening are associated with individual characteristics. If this is the case, the published literature will be consulted to determine if the significant characteristic(s) also impact on the costs and/or quality of life of individuals with diabetes. If so, this will be reflected in the modelling of future costs and quality of life. Sensitivity analysis will be conducted to determine the impact upon cost-effectiveness of changes in the key parameters within the model.

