## Discussion

This study is a novel, randomized controlled trial to investigate the impact of two different types of financial incentives on increasing attendance at diabetic retinopathy screening. The design of the incentives has been based on established principles from behavioral economics [40]. This intervention therefore has the potential to reduce unnecessary sight loss, and to generate large savings in public funds.

Based on the ‘Future Sight Loss’ report [41] and data from the NHS Diabetic Eye Screening website [42], we estimate potential societal savings in the UK of £1.6 million if the £10 is successful in increasing take-up of screening by 10 %. From these reports, it was estimated that 0.94 % of patients are at risk of blindness due to diabetic retinopathy, and the rate of blindness amongst those at risk is 30.5 %. Therefore, if 10 % of the estimated 448,000 individuals with diabetes who fail to attend screening annually were to attend due to the incentive, this would correspond to detection of 423 people who would have been at risk of blindness, and prevention of 129 cases of blindness. Given the annual, per person cost of blindness and sight loss is £12,466 the potential economic savings of reducing screening non-attendance is £1,608,114. The cost of screening the 1,000 study subjects is estimated to be £20,700. The cost of providing a £10 incentive to the total sample will be £10,000. Thus a rough estimate of the overall potential saving, if the study is successful in improving screening, is £1,577,414.

As there is evidence of public support for incentive schemes that are effective and cost-effective [27], if this intervention has the expected impact, it may be an acceptable way to prevent unnecessary blindness due to diabetic retinopathy.

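### The 5-year horizon of the Markov model, taken alone, understates the benefit of the incentives, because gains from averted blindness continue after year 5

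*Protocol article*

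**What the plan says.** All of this is in the protocol article. The fourth research question is "Is offering incentives a cost-effective strategy for enhancing participation", and the text beneath it speaks of value for money. The section on cost-effectiveness analysis answers it in two parts.

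- **Short term:** "the cost per additional screening attendee will be calculated as the cost of screening divided by the observed increase in the number of screening attendees". This is done between every pair of groups.
- **Longer term:** "A longer-term, 5 year, perspective of the cost-effectiveness of the incentives will be assessed using a Markov model". On perspective: "The model will assess the cost-effectiveness from the NHS perspective using the differential rates of screening attendance for each group".

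The inputs taken from the literature are described as "The long-term effects of attending screening in terms of the sensitivity of screening, treatment costs and quality of life", together with the corresponding effects of not attending. The section then states: "The costs across the groups will differ only in the monetary incentives provided". It closes with: "Sensitivity analysis will be conducted to determine the impact upon cost-effectiveness of changes in the key parameters within the model". The horizon is not named among the things to be varied.

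The Discussion prices blindness per year: "Given the annual, per person cost of blindness and sight loss is £12,466".

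**The concern.** Costs and benefits fall at different times. The £10, or the prize draw with the same expected value, is paid once, around the screening visit. The benefit is sight kept, and it accrues in every later year of life. Participants are 16 or older with no upper age limit, and the Background describes retinopathy as a leading cause of sight loss at working age, so some participants will have decades to live.

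A model that stops at 5 years credits a case averted at year 3 with two years of benefit, and a case averted after year 5 with none. The model is the only planned analysis that expresses value in health terms. If its benefit side is cut short, an incentive that is good value could look poor to the policy makers the article names as its audience.

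**Working it through.** **1. The article's own benefit figure (Discussion).**
- People at risk: 448,000 × 10 % × 0.94 % = 421. The article gives 423, which fits rounding of the 0.94 % (44,800 × 0.945 % = 423.4).
- Cases prevented: 423 × 0.305 = 129.
- Saving: 129 × £12,466 = £1,608,114. Less £20,700 and £10,000, this is £1,577,414.

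The figures reproduce. The saving counts one year of cost per case, at a price the article itself calls annual. The article gives no result for the 5-year model.

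**2. Share of blind-years inside the window.** Assumptions, none from the article: onset without screening is uniform over years 0 to 5, life continues L years after onset, and each blind-year carries the same loss. That loss then cancels from the ratio, so its price does not matter.

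Undiscounted, the mean time from onset to year 5 is 2.5 years, so the share is 2.5 / L.

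Discounted at 3.5 % a year, with r = ln(1.035) = 0.0344:

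share = [1 − 5r·e^(−5r) / (1 − e^(−5r))] / (1 − e^(−rL))

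Here e^(−5r) = 0.8420 and 5r = 0.1720, so the bracket is 1 − 0.1720 × 0.8420 / 0.1580 = 0.0835.

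| L (years) | 1 − e^(−rL) | Share, discounted | Share, undiscounted |
|---|---|---|---|
| 5 | 0.158 | 0.529 | 0.500 |
| 10 | 0.291 | 0.287 | 0.250 |
| 15 | 0.403 | 0.207 | 0.167 |
| 20 | 0.497 | 0.168 | 0.125 |

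Cases arising after year 5 are left out of both numerator and denominator. A 5-year model gives them no credit at all.

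**3. Does the result depend on uniform onset?** An annual cohort model followed one at-risk person for 5 and for 40 years. Assumed inputs were a yearly probability of blindness of 30.5 %, 10 %, 5 % or 2 %; mortality of 3 %, 6 % or 10 % a year; later detection of 0 or 10 % a year; and 3.5 % discounting. Only the 30.5 % is in the article (1,280 / 4,200), and reading it as an annual rate for one person is itself an assumption.

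| Share of the 40-year total falling inside 5 years | At 30.5 % a year | Whole grid |
|---|---|---|
| Cases | 86–94 % | 26–94 % |
| Blind-years, undiscounted | 13–33 % | 4–33 % |
| Blind-years, discounted | 21–41 % | 8–41 % |

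At 30.5 % a year, 1 − 0.695^5 = 84 % of at-risk people would go blind within 5 years, before allowing for deaths. Most cases then fall inside the window, while most blind-years fall outside it.

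**4. The cost side.** The section draws treatment costs from the literature but says group costs differ only in the incentives. Read literally, the second statement leaves out the screening of extra attendees (£20,700 / 1,000 = £20.70 each) and their treatment, which favours the incentives. It could also be read to leave out savings from averted blindness. The two statements cannot be netted from the text.

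**The case against.** - **The direction of bias.** A reader might infer that the whole long-term analysis is biased against the incentives, with incentive, screening and treatment costs all counted early. The documents do not support that. The sentence on costs differing only in the incentives may work the other way. Only the effect of the horizon by itself has a clear sign.
- **Cases or blind-years.** A reader might also infer that most cases of blindness are missed. At the article's 30.5 %, read as annual, they are not. Even for blind-years, a majority is not lost if only about 5 years of life remain, and the article describes the eligible group as tending to be the sickest. This limit stands.
- **Extrapolation.** The trial observes attendance at one invitation, and routine yearly invitations carry on for participants. Non-attenders may be detected later and the effect of one visit may fade. A long run that ignores this could overstate benefit. This is a reason to vary later attendance. In the cohort grid, 10 % later detection a year did not bring the captured share of blind-years above 41 %.
- **Perspective.** The £12,466 belongs to an estimate of societal savings, whereas the model takes the NHS view. The figure shows that the article treats the cost of blindness as recurring. It does not give the amount that would enter the model.
- **Condensed article.** Reasons for the horizon, discounting and scenarios may sit in the full protocol, which is not shown. Their absence here is not the point. The 5-year horizon is a stated choice.

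**Conclusion.** The point holds for the horizon taken alone. Stopping at 5 years counts the one-off incentive in full and leaves out quality-of-life gains and avoided yearly costs after year 5, so it understates the benefit of the incentives. With onset spread over years 0 to 5, 3.5 % discounting and 10 to 20 further years of life, about 29 % to 17 % of discounted blind-years from cases arising in the window are captured, and about 53 % with 5 years of life. Every one of these inputs is an assumption.

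The net bias of the whole model cannot be signed until the sentence on group costs is reconciled with the inclusion of treatment costs. The consequence is confined to the long-term part of the fourth research question. The cost per extra attendee, the primary outcome and the first three research questions are unaffected.

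**What to change.** In the section on cost-effectiveness analysis:

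1. Run the same Markov model to a lifetime horizon, or one long enough to capture the consequences of averted sight loss, with costs and outcomes discounted. Report it alongside the 5-year result.
2. In the planned sensitivity analysis, vary later attendance under the continuing yearly invitations and the long-run transition probabilities.
3. State which costs differ between groups, so that the sentence limiting differences to the incentives agrees with the inclusion of treatment costs.

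This needs a change of wording, more model cycles, and long-run progression and mortality inputs from the literature. No trial data collection changes. The downside is more reliance on extrapolated inputs, which is why the 5-year result should stay in the report.

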**Methods:**

This is a three arm randomized controlled trial to investigate the impact of different types of financial incentives (based on principles from behavioral economics) on increasing attendance at diabetic eye screening appointments in London. Eligible participants will be aged 16 or over, and are those who have been invited to screening appointments annually, but who have not attended, or telephoned to rearrange an appointment, within the last 24 months.

Eligible participants will be randomized to one of three conditions:Control condition (usual invitation letter)Fixed incentive condition (usual invitation letter, including a voucher for £10 if they attend their appointment)Probabilistic incentive condition (invitation letter, including a voucher for a 1 in 100 chance of winning £1000 if they attend their appointment).

Participants will be sent invitation letters, and the primary outcome will be whether or not they attend their appointment. One thousand participants will be included in total, randomized with a ratio of 1.4:1:1. In order to test whether the incentive scheme has a differential impact on patients from different demographic or socio-economic groups, information will be recorded on age, gender, distance from screening center, socio-economic status and length of time since they were last screened. A cost-effectiveness analysis will also be performed.

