## Background

Diabetes is an increasing public health concern worldwide, with an estimated 380 million adults with diabetes globally [1]. This corresponds to 8.3 % of the world’s adult population, and is expected to rise to over 10 % by 2035. Recent data suggests that over 4 million people in the UK now have diabetes [2].

All patients with diabetes are at risk of developing diabetic retinopathy. This condition is caused by damage to small blood vessels at the back of the eyes, which reduces the blood supply. This stimulates the growth of fragile, new blood vessels in the eye, which may bleed and damage the retina, leading to sight loss. It is estimated that in England every year 4,200 people are at risk of blindness caused by diabetic retinopathy and there are 1,280 new cases of blindness caused by diabetic retinopathy [3]. It is one of the leading causes of sight loss in the UK in the working population [4] and therefore there is a significant social and financial burden associated with the condition. However, timely diagnosis and treatment can dramatically reduce the risk of blindness.

In England, all people aged 12 years and older with type 1 or type 2 diabetes are offered diabetic retinopathy screening at least annually by the Diabetic Eye Screening Programme (DES). The test involves taking a photograph of the retina, which occurs without contact with the eye. The rate of uptake for screening is 81 % [5], with a range from 7.4 % to 91.8 % across different Primary Care Trusts (PCTs) [6] (excluding the five PCTs with the highest and lowest percentages, the range is 57.7 % to 87.0 %). Therefore, a number of people with diabetes are still not being screened. This puts them at risk of developing avoidable sight loss, and is also a waste of resources in the National Health Service (NHS), due to missed appointments. Although the DES has been an unqualified success, the effectiveness of any program depends on its uptake.

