### Sample size calculation

The primary endpoint is the proportion of the study group who attend their diabetic retinopathy screening appointment. As the study group will comprise patients who have not attended screening for at least two years, including some who have never attended, despite previous interventions to encourage them to attend, this is a very hard to reach population. Attendance in the control group is expected to be extremely low, such as a nominal 1 %. As the eligible study population also tends to be the sickest, with the greatest risk of having retinopathy, and of losing their sight, even a small increase in attendance would have clinical and social benefit.

An increase in attendance of 10 % was deemed clinically significant. A 10 % increase was also considered achievable, as a study found that smoking cessation rates among employees of a large company increased from 5 % to 14.7 % with financial incentives [36], and in another study, warfarin adherence among subjects requiring anticoagulation management improved from 65 % to 97.8 % with a lottery based financial incentive [14]. With two intervention groups, each being compared to the control group, maximum statistical efficiency is achieved by randomising 1.4:1:1. Combining this with an assumed increase in attendance of 10 %, from 1 % in the control arm to 11 % in an intervention arm, there would be 95 % power if 1000 participants were recruited in total (412 in the control group, and 294 in each of the intervention groups). This sample size would also give the study at least 85 % power to detect a smaller increase from 1 % to 7.5 %, which would also be a clinically significant improvement in attendance rates. Should attendance in the control group turn out to be 5 %, the study would still have approximately 85 % power to detect an increase in attendance of 10 % to a level of 15 % in an intervention group [37].

Data from 1st Retinal Screen Ltd suggests that the study group could comprise over 1000 patients. This would allow oversampling at the randomisation stage, so that the intended sample size will still be reached even if participants become ineligible following randomisation (the most common reason for this is most likely to be due to participants attending their routine screening appointments).

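### The cost-effectiveness plan says group costs differ only by the incentive, which contradicts its own attendance-driven model and, taken literally, drops the screening cost of the extra attendees

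*Protocol article*

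**What the plan says.** The Cost-effectiveness analysis section plans two analyses for the fourth research question.

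- **Short term.** A cost per additional attendee for each pair of groups. Its numerator is the cost of screening; the incentive is not named.
- **Long term.** "A longer-term, 5 year, perspective of the cost-effectiveness of the incentives will be assessed using a Markov model". Its input from the trial is attendance: "The model will assess the cost-effectiveness from the NHS perspective using the differential rates of screening attendance for each group". Inputs to be drawn from published literature include "The long-term effects of attending screening in terms of the sensitivity of screening, treatment costs and quality of life", together with the long-term consequences of not attending.

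The paragraph on the long-term model then closes with the cost rule: "The costs across the groups will differ only in the monetary incentives provided".

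The Discussion gives the article's only worked cost figure. It subtracts £20,700 for screening the 1,000 subjects and £10,000 for incentives from a gross saving of £1,608,114, leaving £1,577,414.

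On what the trial observes, the Abstract says that "the primary outcome will be whether or not they attend their appointment". That is attendance following one trial invitation.

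**The concern.** If the groups differ in attendance, and attending leads to a screen and for some people to treatment, then total NHS costs differ between groups by more than the incentive. The closing sentence of the paragraph rules this out. It conflicts with the model's attendance input, with the treatment costs named just before it, with the short-term measure, and with the Discussion.

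The two analyses also define cost differently: the short-term one names screening and not the incentive, while the long-term one admits only the incentive. An analyst who followed the sentence would compute an incremental cost without the screens that the incentive is meant to bring about. That figure would feed the value-for-money answer, which the Background says is meant for policy makers who run screening programmes.

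**Working it through.** **1. The article's own figure.** From the Discussion:

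- 448,000 × 10% × 0.94% = 421 people at risk (stated as 423; the gap does not matter here)
- 423 × 30.5% = 129 cases of blindness
- 129 × £12,466 = £1,608,114
- £1,608,114 − £20,700 − £10,000 = £1,577,414

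The net figure reproduces exactly, and it counts screening and incentives as two separate costs.

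**2. Inputs.**

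- Screening: £20,700 / 1,000 = £20.70 per person (Discussion). *Assumption:* this cost arises when a person attends.
- Incentive: £10 per attender in the fixed-incentive arm (Discussion, Conditions).
- Arm size: 294, since 1,000 / 3.4 = 294 (Sample size calculation). The control rate is applied to the same 294 for a like-for-like comparison.
- Attendance, control versus intervention: 1% vs 11%, 1% vs 7.5%, 5% vs 15% (Sample size calculation).

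**3. Formulas**, with control rate pC and intervention rate pI.

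- Extra attendees E = 294 × (pI − pC)
- Incentives paid I = 294 × pI × £10
- Extra screening cost S = E × £20.70
- Share omitted under the literal rule = S / (I + S)
- Cost per extra attendee = I / E (incentive only) or (I + S) / E (with screening)

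**4. Results, £10 arm, first round.**

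| pC vs pI | E | I | S | S / (I + S) | I / E | (I + S) / E |
|---|---|---|---|---|---|---|
| 1% vs 11% | 29.4 | £323 | £609 | 65% | £11.00 | £31.70 |
| 1% vs 7.5% | 19.1 | £221 | £396 | 64% | £11.54 | £32.24 |
| 5% vs 15% | 29.4 | £441 | £609 | 58% | £15.00 | £35.70 |

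Extra screening is 1.4 to 1.9 times the incentive cost.

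**5. Sensitivity to the assumption in step 2.** Suppose only half of the £20.70 arises on attendance, that is £10.35. The omitted share is then 10.35 / (11.00 + 10.35) = 48% at 1% vs 11%, and 10.35 / (15.00 + 10.35) = 41% at 5% vs 15%. The share reaches zero only if none of the screening cost depends on attendance.

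**6. Years 2 to 5.** The article gives no re-attendance figure, so this is an assumed range. If an extra attendee re-attends each following year with probability q, the screens over five years number 1 + q + q² + q³ + q⁴:

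- q = 0: 1 screen, £20.70
- q = 0.5: 1.94 screens, £40.11
- q = 1: 5 screens, £103.50

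These costs are undiscounted. Later attendance adds screening cost as well as any benefit. Treatment costs cannot be computed, because the article gives no figures.

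**The case against.** The best defence is that the sentence is loosely worded. It may mean only that the cost of delivering the invitation differs by the incentive, with screening and treatment costs following attendance inside the model. The neighbouring sentences and the Discussion make this plausible, and it may well be what was intended. It is not what the sentence says, however: it speaks of costs without qualification and of the incentives as the only difference. A condensed article may leave details out, but this is a positive statement.

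The £20.70 is also open to challenge. It is stated for the whole sample, the trial runs dedicated clinics, and the Background counts missed appointments as wasted resources. Part of the cost may therefore arise whether or not people come. That objection stands as a limit on the size, as step 5 of the working shows, but it does not remove the contradiction.

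A reader might infer four stronger points that the document does not support:

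- **That one attendance will be credited as five years of annual screening, a five-fold overstatement.** The article neither assumes nor excludes persistence. It is a model detail that may sit in the full plan, and sensitivity analysis on key parameters is promised. Five is only the top of an assumed range of 1 to 5.
- **That treatment costs are left out of the plan.** They are named as a model input. The fault is a contradiction.
- **That the errors must favour the incentives.** Omitting screening cost does so. Read literally, though, the sentence would also exclude NHS savings from avoided sight loss, and the article gives no net downstream figure.
- **That disease prevalence comes from literature although** "the eligible study population also tends to be the sickest, with the greatest risk of having retinopathy". The section does not say where prevalence comes from and does not rule out the trial's own screening outcomes.

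**Conclusion.** The concern holds as an internal contradiction in the stated cost rule. Followed literally, the rule omits about 58% to 65% of first-round incentive-plus-screening incremental cost in the £10 arm. This rests on two assumptions: that £20.70 per person arises on attendance, and that the planned attendance rates apply. Total long-term incremental cost could be higher or lower once downstream treatment costs and savings are added. The prize-draw arm is not covered by these figures, because its guaranteed winner changes the incentive cost.

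The attendance assumption for years 2 to 5 is a secondary point for clarification and not an error in the text. It is still worth settling. The trial measures one invitation, screening is offered at least annually, and the Background itself argues that incentives work better for infrequent than for sustained behaviours.

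The primary endpoint and its analysis are unaffected. The answer to the fourth research question is affected.

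**What to change.** Replace the cost sentence with wording such as: *Unit costs and invitation costs are common to all groups apart from the incentive. Screening and downstream treatment costs accrue with attendance in each group, so incremental cost = incentives paid + screening of additional attendees + net downstream costs.*

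Use the same definition, incentive plus screening, in the short-term cost per additional attendee.

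As a secondary clarification, name a one-off-attendance scenario for years 2 to 5 among the planned sensitivity analyses, and charge the incentive in any round in which its effect is credited.

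This changes the model specification only and needs no new data. The small downside is a possibly less favourable cost-effectiveness figure.
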